### Procedures

The OHC will undertake the first counselling session (home visit, expected to last up to 30 minutes) within 4 weeks after consent with two additional counselling sessions, negotiated between the OHC and the study participant as to face-to-face or phone contact, in the first 6 months (expected to last 15–30 minutes). The protocol for MI/AG will be adapted from Weinstein et al. and Plutzer & Spencer [30,34].

The MI/AG approach will follow a structured approach of rapport establishment and identification of oral health and nutritional needs using empathic reflective listening; presentation of menu of options and information with permission; discussion of options and elicitation of “change talk”; elicitation of importance and confidence in behavioural change; the development of behaviour change plan; and a schedule of follow-up. All discussions will be undertaken in a collaborative, person centred approach central to the MI “spirit”. Whilst the menu will present a range of options with potential to affect early childhood dental decay, the discussion will be limited to one or two topics of primary concern to the study participant, in keeping with the MI approach. Negative responses during the counselling session will be accepted without rebuttal and issues left for exploration at a subsequent session. AG will follow the anticipated milestones of teething and transition from wholly breast- or formula-fed to solid foods. Again, topics for discussion will arise in conversation with the study participant with guidance from the counsellor and the counsellor will provide information only when requested to do so. The information will incorporate appropriate dietary and nutritional guidance, following the national guidelines, to assist in the development of healthful behaviours, with the counsellors linking oral and general health impacts of these behaviours [48]. Review of audio recordings of counselling sessions will be undertaken to monitor protocol compliance.

### Sample size and power

Sample size of approximately 514 children in each arm of the trial is required to detect a 35% reduction in dental decay experience [based on decay experience of children within DHS; dmft 1.26 (SD 2.63), test dmft 0.8] with a probability of 0.8 (power 80%) and rejecting the likelihood of no difference at probability 0.05 (α = 0.05) [49]. This is a conservative sample allowance to detect a difference, since an Australian intervention study on early childhood decay found 79% reduction in decay incidence among 20 month-old children [23]. Allowing for drop-off and loss to follow-up over the following 3 years, an initial sample of approximately 750 in each group of the trial would be required (an earlier study of caries prevention within SDS found attrition rate of 9% per annum over two years [50]). The estimated sample size will have a power of 94% to detect a 35% reduction in the prevalence of early childhood decay (dmft > 0; from 0.25 to 0.16) between the groups (α = 0.05). The estimated sample size will also permit detecting a 33% difference in prevalence of overweight or obese children between the two groups (from 20% to 14%) with 80% power and α = 0.05.

Ethical approval for the study has been provided by the University of Western Australia Human Research Ethics Committee (RA/4/1/4469), the Princess Margaret Hospital for Children Ethics Committee (Reg. No. 1900/EP), and the WA Country Health Services Ethics Committee (ref 2011:05). Figure 1 shows the study sample and pathway for the study participants in the test and control arms. All child participants will have the same clinical and other information collected again at approximately 5 years of age. Sample maintenance strategies, including card mail-outs on the child’s birthday, change of address notification and regular updating of the study will be undertaken.

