## Background

There is little information available on the prevalence of early childhood dental decay in Australia. The most recent report on Australian children’s dental health indicated that, among 4-year-olds in 2005, approximately 37 percent of children had at least one decayed baby tooth. On average, there were 1.84 decayed, missing or filled baby teeth (dmft), of which 84 percent comprised of untreated dental decay [1]. In another study, parental report of dental decay experience (cavities, fillings or extractions) among preschool children (aged 2–3 years) was approximately 3% nationally with substantial variation between the States and Territories [2].

Information available from the Western Australian Dental Health Service (DHS) suggests that the majority of children that register with the Service at age five had not attended any dental care facility and were unlikely to have received any specific oral health care information. The mean decay experience (dmft) of WA 5-year-olds in 2009 was 1.26 of which 1.03 (82%) was the “d” component (untreated dental decay) (personal communication: DHS, 2009). One in three 5-year-old children examined in WA was affected by dental decay and one in ten had more than five teeth affected with dental decay, the majority of which was untreated. Severe untreated decay affects a child’s growth, body weight, quality of life as well as cognitive development, and the effects extend beyond the child, to the family, the community and the health care system [3-5].

Data from elsewhere suggest that the decay experience among children is increasing in Australia. A report from South Australia (SA) showed that, for children attending the School Dental Service in SA, the decay experience among 6–7-year-olds in 1998 was 1.16 and nearly doubling to 2.29 in 2008; and among 5-year-olds the decay experience in 2008 was 1.89 of which 1.2 was untreated decay, and 44% of the children were affected with decay [6].

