### Measures

The primary outcome measures are the incidence of dental decay in primary teeth and the prevalence of obesity. Children will be examined at the dental therapy clinics of the DHS of Western Australia for the incidence of dental decay by two blinded, calibrated examiners at 24 and 36 months of age, using the criteria specified by Workshop on Reporting Early Childhood Caries [51] and at 60 months using the criteria of the WHO [52].

Examiner training will involve examination of early childhood decay under the guidance of a specialist paediatric dentist. Further examiner calibration will be undertaken by examination of 10 children consenting to participate in an oral screening program of DHS. During field examinations, approximately 5% of study participants will be re-examined to test for intra- and inter-examiner reliability. Child height/length and weight will be measured and Body Mass Index calculated (BMI; weight/height^2^) and BMI z score determined at 24 and 36 months, using the age-specific WHO growth standards [53]. Number needed to treat as an effect measure of the program will be estimated [54]. Examiner training will be repeated for each cycle of the clinical examinations to maintain reliability over the course of the study.

Secondary outcome measures will be changes in knowledge, attitude, behaviour and self-efficacy of parents towards the oral health of their child and differences in nutritional and dietary patterns between groups. Long-term outcomes will be the incidence of dental decay and referral for care under general anaesthesia among the groups when the child is 5 years of age.

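### The 514-per-arm, 80%-power calculation rests on the dmft of 5-year-olds without saying so: the 80% is unsupported at the 36-month primary examination and falls to about 76% at 60 months.

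*Protocol article*

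**What the plan says.** All references are to the protocol article.

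- **Sample size and power.** The target is stated as "Sample size of approximately 514 children in each arm of the trial", to detect a 35% reduction with 80% power at α = 0.05, "based on decay experience of children within DHS; dmft 1.26 (SD 2.63), test dmft 0.8". The inflation to about 750 per arm is introduced with "Allowing for drop-off and loss to follow-up over the following 3 years" and refers to an earlier study with 9% loss per year. The section adds 94% power for a fall in decay prevalence from 0.25 to 0.16.
- **Background.** "The mean decay experience (dmft) of WA 5-year-olds in 2009 was 1.26". One in three children of that age was affected. For younger children the only figure is parent-reported decay, which "among preschool children (aged 2–3 years) was approximately 3% nationally", with marked differences between States and Territories.
- **Measures.** Decay incidence is a primary outcome, assessed "by two blinded, calibrated examiners at 24 and 36 months of age" and, in the same sentence, at 60 months under different criteria. Decay at 5 years is then listed separately as a long-term outcome.
- **Data analysis.** The decay counts include non-cavitated lesions.

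**The concern.** The control mean and SD belong to children two to three years older than those examined at 24 and 36 months. Because dmft accumulates with age, the control level at 36 months should be lower than at 5 years. For a fixed relative reduction, a lower control prevalence means lower power, and so does a lower mean unless the SD shrinks in proportion.

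The section is not consistent at either age. Read at 36 months, the 3-year attrition allowance fits but the mean and SD do not. Read at 60 months, the mean fits but the attrition allowance stops two years early.

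What is at stake is how a null result is read. A null comparison at 36 months would be taken as coming from a trial with 80% to 94% power, which the document does not establish. The 5-year comparison in aim 4 would be taken as having 80% power when the protocol's own loss rate implies less.

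**Working it through.** **Inputs.** From Sample size and power: means 1.26 and 0.8 (difference 0.46), SD 2.63, α = 0.05 (sidedness not stated; two-sided assumed), 514 evaluable and 750 enrolled per arm, 9% annual loss, prevalences 0.25 and 0.16. From Background: 1.26 is the mean at age 5. Loss is compounded over whole years from enrolment.

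**1. Reproducing the plan's figures.**

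- Means: n = 2(1.96 + 0.8416)² × 2.63² / 0.46² = 513.1, so 514 per arm. This matches.
- Proportions (pooled variance under the null, no continuity correction): 0.25 versus 0.16 at 514 per arm gives 94.8%, against the stated 94%.

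The arithmetic is sound on its own inputs; the question is which age those inputs describe.

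**2. Children remaining per arm.**

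- 36 months: 750 × 0.91³ = 565
- 4 years: 750 × 0.91⁴ = 514
- 60 months: 750 × 0.91⁵ = 468

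Three years of loss would need 514 / 0.91³ = about 683 enrolled, so 750 carries some slack. That slack is used up at four years. Five years would need 514 / 0.91⁵ = about 824.

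**3. 60 months, where 1.26 fits.** Power = Φ(0.46 / (2.63√(2/n)) − 1.96).

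- n = 468: Φ(2.676 − 1.96) = 76.3%
- Prevalence 0.25 versus 0.16 at n = 468: 92.8%

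If 9% of the original sample is lost each year (linear loss), 750 × 0.55 = 412 remain, and the figures are 70.9% and 89.4%.

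**4. 36 months, prevalence.** No control rate for this age is given, so the rates below are assumptions. The relative reduction is the plan's own 0.16/0.25 = 0.64, that is 36%, with 565 per arm.

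| Control rate (assumed) | Intervention rate | Power |
|---|---|---|
| 3% | 1.92% | about 22% |
| 10% | 6.4% | 60% |
| 15% | 9.6% | 79% |
| 20% | 12.8% | 91% |
| 25% | 16% | 96% |

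Power passes 80% at a control rate of between 15% and 16%.

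**5. 36 months, mean dmft.** The control means are again assumptions, with the same relative effect (0.46/1.26 = 36.5%) and 565 per arm. The answer also depends on how the SD changes with the mean:

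| Control mean (assumed) | SD/mean constant | Negative binomial, dispersion (2.63² − 1.26)/1.26² = 3.56 | Variance/mean constant at 2.63²/1.26 = 5.5 |
|---|---|---|---|
| 0.8 | 84% | 80% | 65% |
| 0.5 | 84% | 74% | 46% |
| 0.3 | 84% | 65% | 30% |

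**6. Minor.** 1 − 0.8/1.26 = 36.5%. An exact 35% is a difference of 0.441, which needs 559 per arm and has 76.7% power at 514.

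**The case against.** The strongest reply has five parts.

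- **The 94% does not depend on the 5-year dmft.** This stands. It comes from 0.25 versus 0.16 and is 92.8% at 60 months with compound loss. With the Background's one in three at age 5 and a 35% reduction (0.33 versus 0.2145), it is about 98%. A reader might infer that both stated powers fail at both ages; the document does not support that.
- **Low power at 36 months is not demonstrated.** This also stands. The document gives no examined rate at 36 months. The 3% is parental report of cavities, fillings or extractions, whereas the trial uses calibrated examiners and counts non-cavitated lesions, which should raise the rate. If SD/mean stays constant, power for the mean is not reduced at all. A reader might take the 22% as the trial's real power; it is only the bottom of an assumed range.
- **The effect size is presented as cautious.** The section cites a 79% reduction at 20 months of age in an Australian study. With that effect, 565 per arm would have about 85% power even at a 3% control rate. This is relevant context, but it concerns effect size, not control level, and the stated power is for a 35% reduction.
- **The 60-month examination appears in the same sentence as the 24- and 36-month ones.** The text is ambiguous to that extent, but Measures then classes 5-year decay as long-term. If 60 months were the intended basis, the 3-year attrition allowance would not fit it.
- **35% versus 36.5% is close to rounding.** Agreed: 65% of 1.26 is 0.819. It is a tidy-up only.

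**Conclusion.** The calculation is correct for the inputs used, but those inputs describe 5-year-olds and the section does not say so.

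- **80% for mean dmft:** unsupported at 36 months, because no dmft mean or SD for that age is given. At 60 months it is about 76% with compound 9% annual loss (71% with linear loss).
- **94% for prevalence:** reproduced, and about 93% at 60 months, but tied to a control rate with no stated age or source. At 36 months it would be matched or exceeded near a 25% control rate and would fall well short at 10% or below.

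For 36 months the right word is unsupported, not refuted. The 60-month figure rests on the protocol's own mean, SD, enrolment and annual loss rate, with that rate (observed over two years) assumed to continue for five. Counting whole years from enrolment at 6–12 weeks of age slightly overstates the loss. The error is one of labelling and inputs, but it changes what a null result can be taken to show.

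**What to change.** Revise the Sample size and power section as follows:

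1. State that 1.26 (SD 2.63) is the dmft of 5-year-olds, label the 514-per-arm, 80% calculation as applying to about 5 years of age, and give its power with five years of attrition (468 per arm, about 76%).
2. State the age and source of the 0.25 control prevalence.
3. For the 36-month primary outcome, replace the 80% and 94% claims with power at the expected 565 per arm, over a stated range of 36-month control prevalence and dmft mean and SD. The range should match the trial's case definition, including non-cavitated lesions.
4. Change 35% to 36.5% for the dmft comparison, or give the sample size for an exact 35% (559 per arm).

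The cost is a rewritten paragraph and a short search for age-appropriate rates. Enrolment, examinations and analyses need not change. The stated 60-month power for mean dmft becomes less favourable, and the 36-month power becomes a range.

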There is also a further recognition that oral diseases share risk factors with other chronic diseases and conditions, such as heart disease, cancer, strokes, diabetes and obesity [16]. World-wide and in Australia, a diet-related health concern among children is that of childhood obesity, and in Australia 23% of children aged between 2 and 16 years are overweight or obese [17,18]. Childhood overweight and obesity has a strong association with premature mortality and cardiometabolic morbidity in adulthood [19,20]. A life-course approach to chronic disease development posits the importance of early childhood factors in the development of chronic ill-health, including oral diseases [21].

There is a strong association between dietary factors and oral disease, in particular with dental decay [22], and there are associations between early childhood dietary factors and childhood obesity [23]. Furthermore, an association has been shown between early childhood dietary patterns and dental decay in adolescence and an association between adiposity at adolescence with dental decay [24]. The sharing of risk factors between oral and general health, and the effects of early childhood factors on the later development of diseases points to practical and economic reasons for integrating oral health promotion efforts that can achieve multiple aims during early childhood. For example, the role that periodontal treatment has in glycaemic control among diabetic patients has been highlighted [25] and, general health promotion for positive early childhood nutrition has shown benefits for oral health [26]. Interventions in early childhood are being tested to reduce the prevalence of early childhood obesity [15,27], although effects on oral health have not been reported.

The reported findings in this brief review suggest that the problem of early childhood dental disease requires substantial resources and interventions at a number of levels to manage, and the problem appears to be increasing. The intertwining of risk factors for dental decay and other chronic conditions suggests that health promotion interventions for dental decay may also have effects on other chronic health conditions.

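### The overweight/obesity power sentence is inconsistent as printed (20% to 14% is a 30% reduction with about 70–73% power at 514 per arm), and it powers a broader outcome than the named primary outcome

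*Protocol article*

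**What the plan says.** All references are to the protocol article.

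- Sample size and power sets the evaluable number from the mean decay count: "Sample size of approximately 514 children in each arm of the trial is required to detect a 35% reduction in dental decay experience", with inputs "dmft 1.26 (SD 2.63), test dmft 0.8", 80% power and α = 0.05. Recruitment is then raised to about 750 per arm to allow for losses over three years, citing an earlier attrition rate of 9% a year.
- The same paragraph gives two further statements for the estimated sample size. For decay prevalence: "The estimated sample size will have a power of 94% to detect a 35% reduction in the prevalence of early childhood decay", from 0.25 to 0.16. For weight status: "33% difference in prevalence of overweight or obese children between the two groups (from 20% to 14%) with 80% power", again at α = 0.05.
- Measures states: "The primary outcome measures are the incidence of dental decay in primary teeth and the prevalence of obesity". Data analysis likewise lists obesity prevalence among the binary outcomes for logistic regression and promises prevalence ratios for obesity.
- Background uses the combined category when it gives a national figure: "in Australia 23% of children aged between 2 and 16 years are overweight or obese".

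**The concern.** The weight-status sentence contains a relative difference, a pair of rates and a power. The first two disagree on sight: 6 points out of 20 is 30%. If the 14% is meant exactly, the 80% is too high as well, and the stated chance of missing such an effect (20%) understates the real one. This is one of only two primary outcomes, so the figure is what a reader will use to interpret a null result.

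There is also a difference of category. The power sentence counts overweight and obese children together, while the outcome named as primary and listed for analysis is obesity. These are different binary variables with different prevalences. Left as they are, the two sections do not tell the reader which variable was powered as primary.

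**Working it through.** **Inputs.** From Sample size and power: 514 per arm; dmft 1.26 vs 0.8, SD 2.63; α = 0.05; 94% power for 0.25 vs 0.16; 80% power for 20% vs 14%; 750 recruited per arm; 9% annual attrition. The number of sides for α is not stated and is inferred in step 1.

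**1. Reproduce 514 and fix the sides.** n = 2(z₁₋α/₂ + z₁₋β)² SD²/Δ² with Δ = 1.26 − 0.8 = 0.46:
2 × (1.960 + 0.842)² × 2.63²/0.46² = 513.1, rounded up to 514. A one-sided 0.05 would give 405. The plan is therefore two-sided.

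**2. Reproduce 94% and fix n.** For two proportions with average p̄, power = Φ{[|p₁ − p₂| − 1.960 √(2p̄(1−p̄)/n)] / √([p₁(1−p₁) + p₂(1−p₂)]/n)}. The continuity-corrected version subtracts 1/n from |p₁ − p₂|.

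For 0.25 vs 0.16 at n = 514 this gives 94.8% (93.9% corrected). At n = 750 it gives about 99%. The estimated sample size is thus 514 evaluable per arm.

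**3. Relative difference.** (20 − 14)/20 = 30%. A 33% reduction from 20% leaves 13.4%; a one-third reduction leaves 13.3%.

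**4. Power for 20% vs 14% at 514.** p̄ = 0.17; null standard error √(2 × 0.17 × 0.83/514) = 0.02343; alternative standard error √((0.16 + 0.1204)/514) = 0.02336.
Power = Φ[(0.06 − 1.960 × 0.02343)/0.02336] = Φ(0.603) = 72.7%. The continuity-corrected value is 69.8%; the unpooled and arcsine versions both give 72.9%.

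**5. Number needed for 80%.** n = [1.960 √(2 × 0.17 × 0.83) + 0.842 √0.2804]²/0.06² = (1.0412 + 0.4457)²/0.0036 = 614.1, so 615 per arm; 647 with continuity correction.

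**6. Which intervention rate does give 80% at 514?**

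| Intervention rate | Reduction from 20% | Power, uncorrected | Power, corrected |
|---|---|---|---|
| 14.0% | 30% | 72.7% | 69.8% |
| 13.5% | 32.5% | 79.8% | 77.3% |
| 13.4% | 33% | 81.1% | 78.7% |
| 13.3% (one third off) | 33.3% | 81.9% | 79.6% |

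**7. Could another n rescue 14%?** With three years of loss at 9%, 750 × 0.91³ = 565 and power is 76.6% (74.1% corrected). At 750 it is 87.2%. With two years of loss, 750 × 0.91² = 621 and power is 80.4%, but the paragraph allows for three years, and 621 would put the decay-prevalence power at 97–98% where 94% is printed. One-sided testing at 514 gives 79.8–82.1%, but conflicts with step 1.

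**8. Outcome category.** Obese children are a subset of overweight or obese children, so the control prevalence of obesity is below the 20% assumed. At fixed n and fixed relative reduction, a lower control prevalence gives lower power. The article gives no prevalence for obesity alone, so the loss cannot be calculated.

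**The case against.** The strongest reply is that the three figures can coexist under ordinary rounding. Read as a minimum detectable difference, the calculation from 20% at 80% power and 514 per arm leads to about 13.5%. That prints as 14%, and the corresponding 32.5% prints as 33%. The neighbouring decay-prevalence sentence supports this reading: 0.25 to 0.16 is literally 36% but is called 35%, and an exact 35% reduction (0.25 to 0.1625) has 93.5% power uncorrected, which also prints as 94%. The dmft sentence is equally loose, since 0.46/1.26 is 36.5%.

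This stands as a plausible reconstruction. It is not proof, because both 13.5% and 32.5% lie exactly on a rounding boundary. It does mean that a reader might infer too much in concluding that the trial fails to deliver its stated power. For a true 33% reduction, 514 per arm gives about 79–82%. Only the printed pair of rates falls short.

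The second reply is that obesity may be shorthand for the combined category, with the cut-off left to the full protocol or analysis plan. That is possible, and the absence of a cut-off is not held against the article. The wording still conflicts between sections. A reader might go further and infer that power for obesity alone is very low. The direction is right, but any specific figure needs an obesity prevalence that the article does not give.

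**Conclusion.** The sentence needs correcting. Taken as printed, 20% to 14% is a 30% reduction with 72.7% power at 514 per arm (69.8% continuity-corrected), so the chance of missing it is about 27–30% where the reader is told 20%. The stated 80% belongs to an intervention rate of about 13.3–13.5%. Whether the slip is in the 14% or in the 80% cannot be decided from the article.

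This rests on 514 evaluable per arm and two-sided α = 0.05. Neither is tied explicitly to this sentence, but both are fixed by reproducing the 514 and the 94%.

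Separately, the powered outcome (overweight or obese) is not the outcome named in Measures and Data analysis (obesity). If obesity alone is meant, the printed power does not apply and the true value is lower, by an unknown amount. None of this affects the number to be recruited, which was set by the dmft comparison.

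**What to change.** 1. Replace the figures with one coherent set: either *20% to about 13.4% (33% reduction), about 80% power*, or *20% to 14% (30% reduction), about 73% power at 514 per arm*. State that the test is two-sided and that the basis is 514 evaluable per arm.
2. Use one outcome throughout. Either define the primary outcome in Measures and Data analysis as overweight or obese, to match the power statement, or keep obesity and restate the power for obesity alone, with the assumed control prevalence and its source.

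The cost is wording only. Sample size, allocation and form of analysis are unchanged. The sponsor may have to accept a less favourable stated power or, under the first option in item 2, a broader outcome label.
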